**Fig. 2 Fig2:**
[figure not shown]
Adaptation of immunosuppression in the treatment groups

The TTV load reached after TTV stabilization (expected after 3 months) will be used to guide immunosuppression, which will be tailored according to the scheme above (Fig. 2).

Maintenance immunosuppression will be guided by therapeutic drug monitoring (TDM) of tacrolimus trough levels. Furthermore, signs of toxicity of tacrolimus and cell cycle inhibitors (e.g., leukopenia, gastrointestinal side effects, hypogammaglobulinemia) may lead to dose adaptation and switch between various cell cycle inhibitors.

### Measurements

Most important measurement is creatinine (from blood chemistry) as the key parameter to determine the primary endpoint ΔGFR between randomization and 12 months thereafter.

Another key measurement within this trial is the TTV load in arm 1 patients. TTV load is classified as low with TTV load < 7 log_10_, as medium with TTV load from 7 to 9.5 log_10_, and as high with a TTV load of > 9.5 log_10._

TTV DNA quantitation will be done by TaqMan real-time PCR using probe and primers as described previously [12]. The linear range of TTV quantitation ranges from 2.7 to 10.7 log10 copies/mL as determined by the use of 10-fold dilutions of a plasmid standard. The limit of detection in plasma is 2.7 log10 copies/ml. In each run, a TTV DNA standard and positive and negative controls will be included and any signs of PCR inhibition will be assessed by quantitation of the known amount of control DNA spiked into the samples before DNA extraction [12].

### Outcome assessments

For the primary endpoint ΔGFR between randomization and 12 months thereafter, creatinine from the serum will be measured to calculate GFR (CKD-EPI) at each visit.

The main secondary outcomes are assessed as follows:
GFR (CKD-EPI) at 1 and 2 months after transplantation (screening visits) and 0, 3, 6, 9, and 12 months after randomizationGFR (cystatin) at randomization and 12 months after randomizationProportion of patients with biopsy-proven acute cellular rejection (grade A1 or higher) within 12 months after randomizationProportion of patients with an episode of biopsy-proven lymphocytic bronchitis (grade B1R or higher) within 12 months after randomizationProportion of patients with cytomegalovirus (CMV) infection and number of CMV disease episodes within 12 months after randomizationProportion of patients with community-acquired respiratory viral infection (CARV) within 12 months after randomizationProportion of patients with fungal and bacterial infections within 12 months after randomizationProportion of patients with any of the abovementioned infections within 12 months after randomizationProportion of patients with unscheduled or emergency hospitalizations after randomizationProportion of patients with ICU admissions after randomizationQuality of life (EQ-5D visual analog scale) at screening visits and 0, 3, 6, 9, and 12 months after randomizationProportion of patients with new or progressive malignancy within 12 months after randomizationTacrolimus trough levels at screening visits and 0, 3, 6, 9, and 12 months after randomizationDaily tacrolimus dose [mg] at screening visits and 0, 3, 6, 9, and 12 months after randomizationProportion patients with increased/unchanged/decreased (compared to the previous visit) target trough levels of tacrolimus at screening visits and 0, 3, 6, 9, and 12 months after randomizationExercise capacity measured by the percent predicted distance achieved in the 6-min walk test at randomization and 12 months thereafterCD4 lymphocyte count at 0, 6, and 12 months after randomizationProportion of patients with presence of donor-specific antibodies at 0, 6, and 12 months after randomizationFEV1 in % baseline value at screening visits and 0, 3, 6, 9, and 12 months after randomizationIncidence of chronic lung allograft dysfunction between randomization and 12 months thereafterIgG level at 0, 6, and 12 months after randomizationProportion of patients with rescue immunotherapy (defined by the use of ATG, rituximab, alemtuzumab, plasma exchange, immunoadsorption) between randomization and 12 months thereafter

Data collection time points are displayed in Fig. 3.

**Fig. 3 Fig3:**
[figure not shown]
Data collection time points (SPIRIT figure)

### Statistical analysis

Unblinding procedures are not applicable because the trial is not blinded. Data analysts will be blinded for the randomization results until database closure for the final analysis. Apart from safety reports to the Data and Safety Monitoring Committee (DSMC), no interim analyses are planned.

#### Primary efficacy analysis

The primary efficacy endpoint ΔGFR is defined as the change of the glomerular filtration rate GFR between randomization and 12 months thereafter. GFR will be estimated using the CKD-EPI formula. The primary endpoint analysis will be adjusted for randomization strata and baseline. No subgroup analyses are planned.

An analysis of covariance (ANCOVA) with strata used at randomization and treatment as fixed factors, and the baseline GFR as a covariate is used to test for a difference in location of ΔGFR (in ml/min/1.73 m^2^) between the groups (two-sided at a 0.05 significance level). The analysis of the primary endpoint will be based on the intention-to-treat population.

#### Secondary endpoints

Categorical variables will be reported as absolute and relative frequency, continuous variables by median, mean, standard deviation, 95% confidence interval, minimum, and maximum. Student’s *t* test, analysis of covariance or their non-parametric analogs, as well as chi-square or Fisher’s exact test, furthermore (generalized) linear mixed models will be applied as appropriate for the types of variables, group, high-risk CMV status, and time, as well as a group-by-time interaction term will be used as covariates in the mixed models. All statistical tests will be carried out at a two-sided significance level of 5% without adjustment for multiple comparisons. Full details will be stated in a statistical analysis plan.

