### Randomization

Randomization will be performed centrally via telefax by the Center for Clinical Trials (KKS) of the Philipps-University Marburg for patients matching all eligibility criteria and will be stratified by high-risk CMV status (D+R−) (yes/no) and center using randomization lists generated at KKS with permuted blocks of randomly varying size. The chance for allocation to the control and experimental group is 1:1. Investigators at the participating sites request the randomization result by faxing the completed randomization form, whereupon KKS staff will consult the randomization database and transmit the result to the investigator.

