#### Sample size calculation

The sample size calculation is performed assuming a *t* test of ΔGFR. Because adjusting for stratification factors is assumed to reduce variability, the power for the ANCOVA test of the treatment variable is expected to be rather higher than lower compared to the *t* test.

The sample size calculation is based on the assumption of a mean decline in GFR of 15 between randomization and 12 months thereafter and a standard deviation of 20 in the control group. Two randomized trials [8, 13] observed effect sizes of a similar magnitude. Compared to the control group, a mean decline in GFR of 5 in the experimental group (i.e., difference of 10 in GFR declines between the intervention groups) is regarded as clinically relevant. For a 2-sided significance level of 5% and a power of 80%, 64 patients per group (*n* = 128 in total) are needed to achieve a power of 80% if the true difference in means is 10 and the standard deviation is 20 in both. With an estimated dropout rate of 10%, 144 patients have to be randomized.

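### The tests named for one-per-patient binary secondary endpoints ignore the randomization strata; a stratified test is a free improvement, with a small gain expected mainly for CMV infection

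*Protocol article*

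**What the plan says.** The Randomization section states that allocation "will be stratified by high-risk CMV status" (D+R−, yes or no) "and center using randomization lists generated at KKS with permuted blocks of randomly varying size". With two sites this makes four strata.

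Under Primary efficacy analysis, the ANCOVA for ΔGFR carries the randomization strata as fixed factors. The Sample size calculation adds that adjusting for them should reduce variability.

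The Secondary endpoints section gives a list of methods to be used as appropriate. For categorical outcomes it names two-group tests ("analysis of covariance or their non-parametric analogs, as well as chi-square or Fisher"'s exact test), and then (generalized) linear mixed models with group, high-risk CMV status, time and a group-by-time term. No stratified test for proportions is named, and center is not among the mixed-model covariates. On error control: "All statistical tests will be carried out at a two-sided significance level of 5% without adjustment for multiple comparisons". Details are left to a statistical analysis plan that is not shown.

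**The concern.** Most of the proportions under Outcome assessments are one yes/no result per patient over 12 months: rejection, lymphocytic bronchitis, CMV, respiratory viral, fungal and bacterial infection, hospitalization, ICU admission, malignancy, rescue therapy. The mixed models have time terms and suit repeated measures, such as donor-specific antibodies at three visits. For the single-outcome proportions, chi-square or Fisher's exact test is therefore the natural reading.

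Stratified randomization removes between-stratum variation from the treatment comparison, but an unstratified test still counts that variation as noise. When the strata are prognostic, the test rejects less often than its nominal 5%. Several of these endpoints show whether lower tacrolimus exposure comes at a price in rejection, and the sample was sized for ΔGFR only. For a harm endpoint, a conservative test is not automatically the safe choice.

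**Working it through.** **The plan's own figure.** Inputs from Sample size calculation: "For a 2-sided significance level of 5% and a power of 80%, 64 patients per group", "if the true difference in means is 10 and the standard deviation is 20 in both". Normal approximation: n = 2 × (1.960 + 0.842)² × (20/10)² = 62.8, so 63 per group. The exact t test gives 63.77, so 64, with power 0.801. Dropout of 10%: 64/0.9 = 71.1, so 72 per group and 144 in total. The stated figures reproduce. No power is stated for any binary endpoint, so the rest needs assumed risks.

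**Size of the unstratified chi-square.** Let stratum s have weight w and risk p, with 1:1 allocation balanced within strata and m patients per arm. With no treatment effect:
- variance assumed by chi-square: (2/m) × p̄(1 − p̄), where p̄ = Σwp
- actual variance: (2/m) × Σwp(1 − p)
- ratio R = Σwp(1 − p) / [p̄(1 − p̄)]
- true size ≈ 2Φ(−1.96/√R)

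Assumptions: D+R− share 25%, centers of equal size, risks as shown.

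| Stratum risks | p̄ | p̄(1 − p̄) | Σwp(1 − p) | R | Approx. size |
|---|---|---|---|---|---|
| 15% / 50% by CMV status | 0.2375 | 0.1811 | 0.1581 | 0.873 | 3.6% |
| 15% / 50% by center | 0.325 | 0.2194 | 0.1888 | 0.860 | 3.5% |
| 20% / 40% by CMV status | 0.25 | 0.1875 | 0.1800 | 0.960 | 4.5% |
| 25% / 42% by center | 0.335 | 0.2228 | 0.2156 | 0.968 | 4.6% |

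First row in full: Σwp(1 − p) = 0.75 × 0.15 × 0.85 + 0.25 × 0.50 × 0.50 = 0.0956 + 0.0625 = 0.1581; √0.873 = 0.934; 1.96/0.934 = 2.098; two-sided tail 3.6%.

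Simulation with 128 analysed agrees. At 15%/50%, chi-square size is about 3.6% against 4.7–5.0% for Cochran-Mantel-Haenszel (CMH). With flat or mildly different risks, chi-square size is 4.7–5.2%.

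**Power.** With 128 analysed, stratifying gains 4–5 points at 15%/50%. For CMV infection with a treatment odds ratio of 0.4, chi-square has about 39% and CMH about 44%. In the flat and mild settings the change is between about −1 and +2 points.

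A second simulation used 144 patients, 20,000 trials per scenario, a D+R− share of 20–30%, center odds ratios of 1–2 and a treatment odds ratio of 0.35:
- Rejection, control risk 33% (the Background's one third), CMV-stratum odds ratio 1–2: stratifying changes power by −0.7 to +0.6 points.
- CMV infection, control risk 25% (the upper bound in the Discussion): gain of at most about 1 point at a CMV-stratum odds ratio of 1–2, 2–3 points at 4, and 6–7 points at 8.

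The 15%/50% contrast is an odds ratio of (0.50/0.50)/(0.15/0.85) = 5.7, which lies between the last two.

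**Fisher's exact test.** With no stratum effect its size is 3.2% (128 analysed) or 3.4–3.6% (144). At 144, its power is about 5–7 points below chi-square in every scenario, including those with no stratum effect. Most of its deficit is therefore discreteness.

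**The case against.** The strongest reply is that the article offers a menu, assigns no endpoint to a test, and leaves details to the analysis plan. That is fair, and it is why the absence of an endpoint-by-endpoint assignment is not criticised here. What remains is that the methods actually named for single-outcome proportions are all unstratified, and that the one model option names only one of the two stratification factors.

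A second reply is that any error is toward caution, on secondary endpoints with no power claim and no multiplicity control. This also stands: type I error is not inflated, and the primary analysis is untouched.

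Three stronger readings are tempting and not supported.
- A reader might infer that the trial loses substantial power to see an excess of rejection. That needs a large difference in rejection risk between strata. The article reports none by center or by CMV status. Its remark that control dosing follows center practice makes a center difference conceivable but says nothing about size. A 15% versus 50% contrast between two sites would be an extreme assumption.
- A reader might blame Fisher's low size on the ignored strata. It is present with no stratum effect at all.
- A reader might expect confidence intervals for proportions that are too wide. The Secondary endpoints section lists 95% intervals for continuous variables only; categorical variables get frequencies.

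**Conclusion.** The point holds as a modest efficiency and consistency issue. The named tests for one-per-patient binary endpoints do not follow the stratified design, while the primary ANCOVA does, and center is missing from the mixed-model covariates.

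The cost is conditional on prognostic strata. For CMV infection this is plausible, since D+R− is the article's own high-risk category: chi-square size of about 3.6% and 4–5 points of power at assumed risks of 15% and 50%, and 1 point or less if the stratum odds ratio is 2 or below. For rejection no loss is documented, and over odds ratios of 1–2 it is negligible. Fisher's size of about 3% is a separate matter.

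All of this rests on assumed stratum risks, D+R− share, equal center sizes and treatment effects; the article gives none of them.

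**What to change.** In the statistical analysis plan:
- Analyse the one-per-patient binary secondary endpoints with a Cochran-Mantel-Haenszel test stratified by D+R− status and center, and report a stratified risk difference with 95% CI. Logistic regression with both factors is an equivalent choice.
- For rare events, use exact stratified methods.
- Add center to the covariates of the (generalized) linear mixed models.

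The cost is a few lines of wording before database lock. Both factors are already recorded for randomization, so no new data are needed, and neither the sample size nor the primary analysis changes.

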## Design and participants

The screening of the patients will be performed in two participating study sites (Hannover Medical School and University of Vienna). We assume that screening of 250 patients will result in 144 subjects eligible for the study. The recruitment period is expected to be 39 months.

Selected in- and exclusion criteria are as follows:

Inclusion criteria:
Adult patients 21 to 42 days after de novo lung transplantation (bilateral or combined)Tacrolimus based immunosuppressionDetectable TTV load at randomization (> 2.7 log 10 copies/mL)Women of child-bearing potential: negative serum pregnancy test and highly effective methods of contraception throughout the study.

Exclusion criteria:
History or high-risk of obstructive airway complications after lung transplantationRespiratory failure (need for oxygen therapy or ventilation at screening) inability to undergo transbronchial biopsyAdvanced kidney failure (GFR CKD-EPI < 30 ml/min/1.73 m^2^ at inclusion and/or current renal replacement therapy at inclusion or randomizationAdvanced liver cirrhosis (CHILD-Pugh Score C) after lung transplantationFluctuating tacrolimus drug levels (less than 20% in target range after transplantation)Symptoms of significant mental illness with the inability to cooperate or communicate with the investigatorUnlikeliness to comply with the study requirementsHIV positivity

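### The covariates listed for the secondary mixed models include CMV status but omit center and the baseline value, which costs precision and makes some tests mildly conservative

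*Protocol article*

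**What the plan says.** Under *Randomization*, the protocol article stratifies by high-risk CMV status and by "center using randomization lists generated at KKS with permuted blocks of randomly varying size". There are "two participating study sites" (*Design and participants*).

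Under *Primary efficacy analysis*: "The primary endpoint analysis will be adjusted for randomization strata and baseline". Under *Sample size calculation*, the article argues "Because adjusting for stratification factors is assumed to reduce variability" and concludes that the ANCOVA should have at least the power of the t test.

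Under *Secondary endpoints*, the covariate list is shorter: "group, high-risk CMV status, and time, as well as a group-by-time interaction term will be used as covariates in the mixed models". The same paragraph sets the error level ("All statistical tests will be carried out at a two-sided significance level of 5% without adjustment for multiple comparisons") and ends "Full details will be stated in a statistical analysis plan".

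*Outcome assessments* lists several repeated outcomes (CKD-EPI GFR, EQ-5D visual analog scale, tacrolimus trough level and dose, FEV1) at screening visits and at months 0, 3, 6, 9 and 12 after randomization.

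**The concern.** The article names one of its two strata in the mixed models and leaves out the other without giving a reason. It also names no baseline covariate. Both choices depart from the primary analysis and from the article's own argument for adjusting.

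Allocation is balanced within center. A model that ignores center therefore puts the between-center difference into the residual variance, while the estimated group difference does not vary because of it. The reported standard error is then too large and the test rejects less often than its nominal level. Leaving out a baseline that is correlated with follow-up discards precision.

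A center difference is plausible for some outcomes. Control-arm dosing partly follows local practice, and the starting tacrolimus target depends on alemtuzumab induction (*Follow-up protocol*). The article does not say whether induction use differs between the sites.

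The abstract hopes for less toxicity at similar efficacy. The primary endpoint covers toxicity, so the efficacy side rests on secondary outcomes such as FEV1. Needlessly wide intervals make a loss there harder to see.

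**Working it through.** **The plan's own figure.** No figure is given for the secondary models. The primary sample size reproduces. With a difference of 10, SD 20, two-sided 5% and 80% power, 2 × (1.96 + 0.8416)² × 20²/10² = 62.8, so 63 per group by the normal approximation. The t test has 79.5% power at 63 and 80.1% at 64. Then 64/0.9 = 71.1, so 72 per group and 144 in total. This point does not touch that figure.

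**Omitting center, group difference at one visit, no baseline.** Let p be the share of patients in one center and D the center gap in residual SDs. D is not in the article and is assumed. Under center-stratified 1:1 allocation:

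- SE ratio k (without / with center) = √(1 + p(1−p)D²)
- actual type I error = 2 × (1 − Φ(1.96k))
- power, where the adjusted test has 80%, = Φ(2.8016 − 1.96k)

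With p = 0.5:

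| D | k | Type I error | Power |
|---|---|---|---|
| 0.2 | 1.005 | 4.9% | 79.7% |
| 0.5 | 1.031 | 4.3% | 78.3% |
| 0.8 | 1.077 | 3.5% | 75.5% |
| 1.0 | 1.118 | 2.8% | 72.9% |

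With a 70:30 split, k runs from 1.004 to 1.100 and type I error from 4.9% to 3.1%.

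Simulation (2,500 trials, N = 144, two equal centers, stratified blocks, correlation 0.6) agrees. At D = 1.0 without center, the mean model SE was 0.186 against an empirical 0.164, with type I error 2.3%. With center these were 0.166, 0.164 and 4.8%. At D = 0.2 there was no visible difference.

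**Omitting center, change from month 0.** A constant center effect cancels within each patient. In 60 fitted random-intercept models with D = 0.5, the month-12 group-by-time estimates were identical with and without center, and the SE was 0.1485 both ways. In the simulation above, type I error for this contrast was 5.1% to 5.5% either way.

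**Omitting baseline.** Let r be the correlation between month 0 and month 12, also assumed, with equal variances at the two visits. Relative variances of the month-12 contrast are 1 (follow-up only), 2(1−r) (change from month 0) and 1−r² (baseline-adjusted). SE ratios are the square roots of their quotients:

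| r | Change 2(1−r) | Adjusted 1−r² | SE, follow-up only / adjusted | SE, change / adjusted |
|---|---|---|---|---|
| 0.5 | 1.00 | 0.75 | 1.15 | 1.15 |
| 0.6 | 0.80 | 0.64 | 1.25 | 1.12 |
| 0.7 | 0.60 | 0.51 | 1.40 | 1.08 |
| 0.8 | 0.40 | 0.36 | 1.67 | 1.05 |

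All three contrasts have valid standard errors; they differ only in precision. With baseline as a covariate, omitting center matters less: at D = 1.0 and r = 0.6 the simulated model SE was 0.1368 without center and 0.1335 with it.

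**The case against.** The strongest defence is that the paragraph is a condensed list of methods and defers its details to the analysis plan. Random effects, response rows and the reported contrast are normal content for that plan, and their absence here is no fault. That stands. What remains is the covariate list itself: it is published, it names one stratum and not the other, and the analysis plan would have to go beyond it.

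The defence is also right that part of the need is already met. Month-12 change in CKD-EPI GFR is the primary endpoint and is fully adjusted, FEV1 is expressed relative to a baseline value, and analysis of covariance is among the methods named for secondary endpoints.

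A reader might infer more than the article supports:

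- **That the error bars are wrong in general.** Omitting baseline leaves them valid. Omitting center only widens them, and not for the change contrast.
- **That 33% to 96% more patients would be needed without baseline** (1/0.75 to 1/0.51, for r = 0.5 to 0.7). This applies only if month 0 plays no part in the contrast. If month 0 is a response row, the group-by-time contrast already uses it, and the figure is 33% to 18% (1.00/0.75 to 0.60/0.51).
- **That screening and month-0 visits will be response levels.** The article gives measurement times and does not say which rows enter the model.
- **That the chi-square and Fisher tests for binary endpoints must be replaced.** That is a separate question, and nothing here quantifies it.

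**Conclusion.** The inconsistency is in the text and worth correcting, but its effect is modest. The secondary mixed models as listed are less precise than they could be. For a between-group contrast at a visit they are also mildly conservative: the SE is 0.5% to 12% too large and a 5% test runs at 4.9% to 2.8%, over assumed center gaps of 0.2 to 1.0 SD with equal centers. The upper end needs the two sites to differ by a full residual SD, which nothing in the article establishes. For change from month 0, a constant center effect costs nothing, and baseline adjustment would still lower the SE by a factor of 1.15 to 1.05 for r = 0.5 to 0.8. Against a follow-up-only contrast the factor is 1.15 to 1.67.

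The ranges for D and r, the equal correlation between visits and the restriction to continuous outcomes are assumptions of this check. No result would be invalid.

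**What to change.** In *Secondary endpoints*, add center as a fixed effect beside CMV status. State how the month-0 value is used, by one of two sound options:

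1. Month 0 as a covariate, with only the visits at months 3, 6, 9 and 12 as outcomes.
2. Month 0 as a response, with the group means constrained to be equal at that visit.

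In either case, name the month-12 group difference as the reported effect.

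The cost is a change of analysis wording. Center and the month-0 values are already collected, and no visit, patient or procedure is added.
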